# IMproving facial PRosthesis construction with contactlESs Scanning and Digital workflow (IMPRESSeD): study protocol for a feasibility crossover randomised controlled trial of digital versus conventional manufacture of facial prostheses in patients with orbital or nasal facial defects

**DOI:** 10.1186/s40814-023-01351-w

**Published:** 2023-07-03

**Keywords:** Maxillofacial prosthesis, Head and neck neoplasms, Computer-aided design, Three-dimension printing, Feasibility studies, Cross-over studies, Randomised controlled trial, Qualitative research, Technology assessment, Biomedical

## Abstract

**Background:**

Facial prostheses can have a profound impact on patients’ appearance, function and quality of life. There has been increasing interest in the digital manufacturing of facial prostheses which may offer many benefits to patients and healthcare services compared with conventional manufacturing processes. Most facial prosthesis research has adopted observational study designs with very few randomised controlled trials (RCTs) documented. There is a clear need for a well-designed RCT to compare the clinical and cost-effectiveness of digitally manufactured facial prostheses versus conventionally manufactured facial prostheses. This study protocol describes the planned conduct of a feasibility RCT which aims to address this knowledge gap and determine whether it is feasible to conduct a future definitive RCT.

**Methods:**

The IMPRESSeD study is a multi-centre, 2-arm, crossover, feasibility RCT with early health technology assessment and qualitative research. Up to 30 participants with acquired orbital or nasal defects will be recruited from the Maxillofacial Prosthetic Departments of participating NHS hospitals. All trial participants will receive 2 new facial prostheses manufactured using digital and conventional manufacturing methods. The order of receiving the facial prostheses will be allocated centrally using minimisation. The 2 prostheses will be made in tandem and marked with a colour label to mask the manufacturing method to the participants. Participants will be reviewed 4 weeks following the delivery of the first prosthesis and 4 weeks following the delivery of the second prosthesis. Primary feasibility outcomes include eligibility, recruitment, conversion, and attrition rates. Data will also be collected on patient preference, quality of life and resource use from the healthcare perspective. A qualitative sub-study will evaluate patients’ perception, lived experience and preference of the different manufacturing methods.

**Discussion:**

There is uncertainty regarding the best method of manufacturing facial prostheses in terms of clinical effectiveness, cost-effectiveness and patient acceptability. There is a need for a well-designed RCT to compare digital and conventional manufacturing of facial prostheses to better inform clinical practice. The feasibility study will evaluate key parameters needed to design a definitive trial and will incorporate early health technology assessment and a qualitative sub-study to identify the potential benefits of further research.

**Trial registration:**

ISRCTN ISRCTN10516986). Prospectively registered on 08 June 2021, https://www.isrctn.com/ISRCTN10516986.

## Background

Head and neck cancer (HNC) is the eighth most common cancer in the United Kingdom (UK) [1]. Incidence rates have increased by 34% over the last 3 decades and around 12,400 new cases are diagnosed each year [1]. HNC is commonly diagnosed at a late stage with advanced disease and primary cancer treatment may involve surgery, radiotherapy and/or chemotherapy [1, 2]. Cancer treatment can have numerous consequences due to the complexity of head and neck anatomy and may result in the complete or partial loss of a facial part [3, 4]. The resulting facial defects may be surgically reconstructed or prosthetically rehabilitated using silicone facial prostheses.

A facial prosthesis is a removable replacement for a facial part which may help to improve a patient’s appearance, function, comfort and quality of life [5, 6]. Facial prostheses may be provided for a variety of conditions and conservative estimates suggest over 2000 prostheses are made each year in the UK [7]. Facial prostheses will deteriorate over time, for example through colour change or physical degradation [8, 9]. Furthermore, patients may exhibit seasonal changes to their complexion or physical changes to their soft tissues during healing. Therefore, facial prostheses require regular refurbishment and replacement on a 6- to 24-month basis which presents a long-term impact on both patients and healthcare services [9].

Conventional manufacturing of facial prostheses involves multiple clinical and laboratory procedures including a facial impression, handcrafting a wax pattern and manually converting the wax pattern into a silicone prosthesis [10]. Conventional manufacturing processes can have a variety of limitations from both the patient and healthcare service perspective. For example, large facial impressions can be uncomfortable or claustrophobic for patients and may distort the soft tissues which could impair final prosthetic fit [11–13]. It has been suggested that it will take approximately 9 to 10 h to manufacture a facial prosthesis with the manufacturing costs estimated to be in the region of £1000 to £1500 at one UK hospital [6, 14, 15]. Consequently, conventional manufacturing of facial prostheses is considered to be time, labour and skill intensive [10, 12, 16, 17]. The final result will depend upon many patient and service factors including the maxillofacial prosthetist’s skills and experience [12, 16].

There has been increasing interest in the use of computer-aided design and computer-aided manufacturing (CAD-CAM) technologies for facial prosthesis manufacture in recent years [18]. A systematic review has illustrated that a wide variety of digital techniques have been applied to different stages of facial prosthesis manufacture [19]. These techniques may offer many benefits to patients and healthcare services for example, 3D facial scanning could be a contactless, comfortable and accurate alternative to facial impressions [12, 13]. CAD processes could reduce dependence on the maxillofacial prosthetist’s skills, speed up the prosthesis design stage and enable patients to input through real-time adjustments [16]. Digital skin colour measurements and colourant recipes may help to improve the objectivity and efficiency of colour matching [17, 20, 21]. CAM processes could offer efficiencies in the time and number of stages for production although it is acknowledged that facial prosthesis manufacture has not yet shifted to complete digital fabrication [16, 19, 22–24]. Whilst a broad range of technologies have been introduced to facial prosthesis manufacture, there is currently no single set of standards exclusive to digitally manufactured facial prostheses [19].

A recent systematic review of the outcome measures used in facial prosthesis research found that clinical research in this area was largely restricted to observational studies and only identified 2 previously published randomised controlled trials (RCTs) [25]. Kiat-Amnuay et al. conducted a multicentre crossover RCT which focussed on facial prosthesis materials [26, 27]. During the study, duplicated moulds were used to produce 2 prostheses from silicone and chlorinated polyethylene elastomer materials [26, 27]. Their RCT was terminated early following the recruitment of 42 participants due to recruitment futility resulting from strict eligibility criteria [26]. Abd El Salam et al. conducted a pilot crossover RCT with a small number of participants which compared conventional manufacture of orbital prostheses with a technique involving rapid prototyping [23]. Although the intervention prostheses were designed based on mirroring techniques and manufactured based on the fused deposition modelling of prosthesis replicas, the authors processed the intervention and control prostheses on casts poured from the same impression [23]. Very specific clinical applications of digital technology had been explored as the fit of their intervention prostheses would still be based upon conventional impression processes. Therefore, there remains a need to formally evaluate the clinical application of digital technology more broadly across 3D facial scanning, CAD and CAM.

Furthermore, there has been limited consideration of the health economic impact of facial prostheses interventions [25]. The manufacturing times and costs reported in the literature are often stated without presenting formal evaluations or are based upon the findings of case reports [6, 14, 15]. Studies that capture health-related quality of life, health utility or costs could help generate evidence to support health economic evaluations [25]. Faris et al. evaluated the health utility of different health states with naïve observers and reported visual analogue scale, standard gamble and time trade off derived health utilities for the post-rhinectomy nasal defect, postsurgical reconstruction and post-prosthetic rehabilitation [28]. Ryan et al. conducted a retrospective observational study to compare costs to the hospital associated with auricular reconstruction with either autologous repair or implant retained prostheses [29]. Further studies are required that collect robust data on both the costs and outcomes associated with different methods of facial prosthesis manufacture to inform cost effectiveness analysis.

Consequently, there is a need for a well-designed RCT to compare the clinical and cost-effectiveness of digitally manufactured versus conventionally manufactured facial prostheses. An initial feasibility RCT would provide crucial information about the key parameters needed to plan a definitive trial. Early health technology assessment could support health economic evidence development during the early stages of clinical research and help prioritise future research needs [30]. Furthermore, qualitative research with patients could provide insight into the lived experience of facial prosthesis manufacturing processes and help evaluate the potential application of digital technology from a patient perspective.

## Methods

### Objectives

The aim of the IMPRESSeD study is to determine if it is feasible to conduct a future definitive crossover RCT to evaluate the clinical and cost-effectiveness of digitally manufactured facial prostheses with conventionally manufactured facial prostheses in patients with orbital and nasal facial defects. The primary objective of the study is to assess eligibility, recruitment, conversion and attrition rates.

The secondary objectives are to:Investigate the acceptability of the study design and interventionMeasure key outcome domains relating to preference, health-related quality of life, manufacturing time and costs to synthesise data to inform the sample size of a definitive trialDetermine the feasibility of the outcome measures as a method to measure the effectiveness of the trial treatments within a definitive trialDetermine the feasibility of running a multicentre RCTEvaluate the feasibility of delivering various components of the intervention within a protocolDevelop, populate and evaluate an early-stage health economic evaluation:Identify and evaluate the main drivers for cost-effectiveness using available evidenceExplore and evaluate model uncertainty using the value of the information frameworkDetermine optimal decision within the health economic framework for making decisions under uncertaintyUndertake a qualitative sub-study to explore patients’ perception, experience and preference of the 2 different methods of facial prosthesis manufacture

### Trial design and study setting

The IMPRESSeD study is co-designed with Patient and Public Involvement and Engagement (PPIE) contributors who wear facial prostheses and the SMILE AIDER PPIE Forum which ensures the study addresses questions of importance to participants and maximises patient benefits. The study design is a multi-centre, 2-arm, crossover, feasibility RCT with early health technology assessment and qualitative research. All trial participants will receive 2 new facial prostheses which will be manufactured using digital and conventional manufacturing methods.

Participants will be recruited from the Maxillofacial Prosthetic Departments of participating UK National Health Service (NHS) hospitals which includes Leeds Teaching Hospitals NHS Trust and Guy’s and St Thomas’ NHS Foundation Trust. Under usual care at the NHS hospitals, maxillofacial prostheses are provided free of charge to patients through the centrally funded NHS system. Therefore, provision of the conventional prostheses will be attributed to NHS Treatment Costs [31]. Provision of the intervention prostheses will be a Research Cost and will be supported by the research funders, Sponsor and NHS sites [31].

The 2 prostheses will be made in tandem and marked with a colour label to mask participants to the manufacturing method. The order of receiving the intervention will be allocated using minimisation, a widely accepted alternative to randomisation which is effective in minimising imbalance in the treatment groups across key characteristics in RCTs with small sample sizes [32]. Given the variability of the study population, for example, in the extent of facial defect or type of prosthesis being provided, a crossover design will help minimise the risk of confounding as both manufacturing processes are evaluated with the same participant with each participant acting as their own control [33]. A further advantage of crossover study designs is that fewer study participants are required to obtain the same precision in the estimation of intervention effects compared to a standard parallel study design [33].

Following the 4-week follow-up with the first prosthesis, participants will receive the second prosthesis and the first prosthesis will be retained at the site until the final review visit. A washout period was not deemed necessary as it was anticipated that any effects of the prosthesis on health-related quality of life would be temporary whilst the prosthesis was in regular use and hence carry-over effects were not expected to influence outcomes in the second period [33]. A similar crossover design has been used successfully in RCTs of facial prostheses and complete denture manufacturing [23, 26, 27, 34].

### Eligibility criteria

The inclusion criteria comprise patients who have acquired orbital or nasal facial defects and require a replacement facial prosthesis. Patients must also be capable of giving informed consent, aged 16 years or above and available for follow-up. The feasibility study will initially recruit patients with HNC. The Trial Management Group (TMG) will review recruitment and may consider including patients with other acquired conditions as they will be treated within the same services with the same interventions. The exclusion criteria reflect the appropriateness of a crossover design in evaluating interventions in the treatment of stable, chronic conditions [33]. Exclusion criteria therefore include patients who are receiving active cancer therapy, have plans for major reconstructive surgery or have not received a removable facial prosthesis previously. Patients will also be excluded if they have facial defects due to an underlying congenital aetiology, have known hypersensitivity to the materials used in the research, have pre-existing skin conditions that prevent the delivery of a new prosthesis or are unable to give informed consent.

### Interventions

Each participant will have an intervention and control prosthesis made in tandem by maxillofacial prosthetists. The control facial prosthesis will be produced through conventional manufacturing methods (current standard of care) involving a facial impression, handcrafting a wax pattern and converting the wax pattern into a silicone prosthesis. The intervention facial prosthesis will involve 3D facial scanning and CAD-CAM. Both prostheses will be colour matched using the same digital skin colour measurements and colourant recipe and both moulds will be packed with the same silicone. The prostheses will also include the same implant components (where applicable) and duplicate ocular components for orbital prostheses. The ocular components will be manufactured using the same technique (either using hand painting or digital photographic techniques) according to the maxillofacial prosthetist’s usual standard of care [35]. Members of the research team at the University of Leeds will be involved in the digital design of the intervention facial prostheses; however, the maxillofacial prosthetist will be responsible for finishing, quality assuring and delivering the intervention. There are no criteria for discontinuing or modifying the allocated interventions for a trial participant however participants may be withdrawn for appropriate medical reasons and participants are free to withdraw from the study at any time.

The workflow for manufacturing the intervention facial prosthesis has been informed by a review of the literature and tested during a preclinical laboratory study. 3D facial scanning will be undertaken using a structured light scanner (Artec Space Spider; Artec 3D) which will capture the participant’s facial defect and surrounding facial features. Whilst a broad range of facial scanning techniques are available [19, 36], structured light scanning has been shown to have good accuracy and repeatability at digitising facial defects in an in vitro context [37–39]. CAD will involve the use of a 3D Morphable Face Model (Leeds Face Model; University of Leeds) to help design the facial prosthesis in a statistically meaningful way based upon the participant’s other facial features [40–42]. There will be opportunity to further modify the design using landmark fitting techniques where participants share facial photographs from before their cancer treatment or wearing a previously successful prosthesis [43]. Models of the participant’s facial features and positive or negative prosthesis replicas will be printed in an appropriate resin material (such as Model V2 Resin; Formlabs) at a resolution of 50 μm using a stereolithographic desktop 3D printer (Form 3; Formlabs). Direct silicone printing is not yet suitable for printing definitive prostheses due to limitations in the layer thickness [24]. Instead, the prosthesis replicas will be converted to wax and modified by the maxillofacial prosthetist to ensure marginal adaptation and to add thin margins, additional detail and fine textures [23]. Once approved by the maxillofacial prosthetist and participant, the intervention wax pattern will be converted into a silicone material (such as M511 Maxillofacial Silicone; Technovent Ltd) using standard procedures.

### Outcomes

Primary feasibility outcomes include the proportion of patients approached that were eligible (eligibility rate), invited that were successfully recruited (recruitment rate), eligible that consented (conversion rate) and recruited that dropped out of the study (attrition rate).

Secondary feasibility outcomes include:Differences in recruitment rates between sitesCompletion rates, missing data, estimates, variances and 95% confidence intervals for the outcome measures relating to preference, health-related quality of life, timing data and costsNumbers of adverse events (AEs) and adverse reactions (ARs)Factors related to trial delivery, e.g. success of minimisation, fidelity of masking, compliance with trial schedule, acceptability of the intervention and components of the protocol working together

Health economic feasibility outcomes include:Cost per Quality Adjusted Life Year (QALY) on current evidenceIdentification of future research needs via Value of Information framework

### Outcomes for the definitive trial

Outcomes for the definitive trial are anticipated to include participant preference, generic health-related quality of life, condition-specific quality of life and costs from the healthcare perspective. The outcome measures have been chosen based upon a systematic review of the facial prosthesis literature and include participant preference, the Short Form-12 (SF-12v2), EQ-5D-5L, the Toronto Outcome Measure for Craniofacial Prosthetics (TOMCP-27) and resource use questionnaires [25]. Table 1 provides a summary of the planned outcomes and outcome measures to be used in the study along with ideal and maximum timepoints for evaluation.

**Table 1 Tab1:** Timepoints for collection of outcome measures

Outcome	Outcome Measures	Ideal timepoint of evaluation	Maximum timepoint of evaluation
Participant preference	Participant preference for control or intervention prosthesis captured on CRFs	4 weeks after delivery of the second prosthesis	8 weeks following delivery of the second prosthesis
Condition specific quality of life	TOMCP-27	Baseline	Prior to delivery of either prosthesis
		4 weeks after delivery of each prosthesis	8 weeks after delivery of each prosthesis
Generic health-related quality of life	SF-12v2 and EQ-5D-5L	Baseline	Prior to delivery of either prosthesis
		4 weeks after delivery of each prosthesis	8 weeks after delivery of each prosthesis
Costs from the healthcare perspective	Resource use questionnaire	Timing and consumable data collected at each clinical visit or laboratory stage	1 week after each clinical visit or laboratory stage
Participants’ perception, lived-experience and preference of the two methods of making facial prostheses	Semi-structured interviews (qualitative sub-study)	Sampled across the IMPRESSeD study visits or within 12 months of study completion	Broad time frame helpful to identify what is important to patients whilst going through the manufacturing process and when reflecting on processes in retrospect

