### Sample size

The feasibility study will estimate treatment effects and variances to inform the sample size of a definitive trial. As there have been very few crossover RCTs in this research area, there was insufficient data available to base the sample size calculation upon the proposed sample size for a definitive trial [47]. The sample size was therefore based upon general recommendations for feasibility studies and a sample size of up to 30 participants was chosen to address the study objectives [48]. It was acknowledged that as the IMPRESSeD study has a crossover design, it would likely have greater power than a parallel-group study and therefore may not need to recruit as many participants as suggested in these general recommendations [49]. Furthermore, consideration was given to the anticipated attrition rates. A dropout rate of up to 33% might be anticipated based upon the findings of a previous crossover RCT comparing facial prosthesis materials [26]. It was noted however that this previous study had a significantly longer follow-up period compared with the IMPRESSeD study (4 months compared to 4 weeks for each prosthesis). The IMPRESSeD study has embedded PPIE into study design and delivery to minimise attrition.

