### Data collection methods

Data will be collected during clinical visits and laboratory stages using CRFs and standardised questionnaires. Data will be collected at baseline and prespecified time points as illustrated in Table 1. Investigators will check CRFs and questionnaires for missing data upon completion. The forms will also be reviewed by the trial coordinator and data queries will be sent to the site for resolution if any data is missing. Investigators may also contact participants over the phone to complete questionnaires to maximise data completeness and maintain data collection time-points. If a participant withdraws from the IMPRESSeD study, any identifiable data will be removed; however, anonymised data will be retained.

Participant preference will be used to indicate whether patients prefer facial prostheses produced by conventional or digital manufacturing methods in a similar way to a study of facial prosthesis retention systems [51]. The TOMCP is a condition-specific quality of life instrument that has been evaluated for reliability and validity during a crossover RCT of facial prosthesis materials [27]. The reduced 27-item, 9-domain version will be used to minimise participant burden [27]. Two generic instruments (SF-12v2 and EQ-5D) have been selected to capture information about health-related quality of life and will also be used to inform the early health technology asssessment [52]. The SF-12v2 is a reliable and valid measure of physical and mental health and the SF-12 has previously been used in studies of auricular prostheses [53–55]. It covers 8 domains which include physical functioning, bodily pain, general health, vitality, social functioning, mental health and role participation with physical and emotional health problems. The EQ-5D is the National Institute for Health and Care Excellence’s preferred measure of health-related quality of life in adults which captures information on 5 dimensions of mobility, self-care, usual activities, pain or discomfort, and anxiety or depression [56]. The responses can be combined into a 5-digit number to describe the participant’s health state. Furthermore, the EQ-5D visual analogue scale captures participants’ self-rated health. The 5-level EQ-5D version will be completed and a cross-walk or further algorithm update will be used to derive utility values [56–58].

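### The 8-week limit for first-period questionnaires is not capped at delivery of the second prosthesis, so a form retrieved after an on-time switch counts as in window while the other prosthesis is worn

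*Protocol article*

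**What the plan says.** Table 1, under Outcomes for the definitive trial, gives the quality-of-life questionnaires an ideal time of "4 weeks after delivery of each prosthesis" and a maximum of "8 weeks after delivery of each prosthesis". One rule covers both prostheses. The baseline row of the same table is limited by an event instead: "Prior to delivery of either prosthesis".

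The abstract sets the review schedule: "Participants will be reviewed 4 weeks following the delivery of the first prosthesis and 4 weeks following the delivery of the second prosthesis". Trial design and study setting places the crossover: "Following the 4-week follow-up with the first prosthesis, participants will receive the second prosthesis and the first prosthesis will be retained at the site", where it stays until the final review. There is no washout, on the ground that "any effects of the prosthesis on health-related quality of life would be temporary whilst the prosthesis was in regular use".

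Data collection methods describes collection at clinical visits and laboratory stages. Investigators check forms on completion, and the trial coordinator reviews them and sends queries to the site when data are missing. It adds: "Investigators may also contact participants over the phone to complete questionnaires to maximise data completeness and maintain data collection time-points".

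The section on sample size states what the scores are for: "The feasibility study will estimate treatment effects and variances to inform the sample size of a definitive trial".

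**The concern.** In a crossover, a first-period score is informative only if it is taken while the first treatment is in effect. Here the first treatment ends at an identifiable event, the hand-over, yet the window for the first-period questionnaires is set by the calendar alone. The authors used an event limit for the baseline forms but not at the other point where an event ends the valid period.

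The protocol's own argument for having no washout makes this matter. If effects last only while a prosthesis is in use, a first-period form completed after the switch describes either the second prosthesis or a recollection of the first. Labelled as first-period data, it pulls the estimated difference between prostheses towards zero and disturbs the within-person variance. It also counts as a completed, on-time form, so the completion rate looks better than the usable data justify. These estimates, variances and completion rates are listed among the secondary feasibility outcomes and are meant to inform the definitive trial.

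**Working it through.** The plan states no figure to reproduce for this point. The sample size of up to 30 rests on general recommendations for feasibility studies, not on a formula. The check is a calendar, followed by an illustration of size.

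**1. Calendar.** Count weeks from delivery of the first prosthesis. Inputs are an ideal time of week 4 and a maximum of week 8 (Table 1), with delivery of the second prosthesis following the review (Trial design and study setting). Assume delivery takes place at the review. If it comes somewhat later, the overlap is shorter.

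Weeks in which a first-period form is in window after the switch = max(0, 8 − week of second delivery):

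- review and delivery at week 4: 8 − 4 = 4 weeks
- week 5: 3 weeks
- week 6: 2 weeks
- week 7: 1 week
- week 8: 0 weeks

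With everything on time, week 8 is both the last permitted date for the first-period form and the ideal date for the second-period form (4 + 4 = 8). These intervals matter only for forms not completed at the review. A form completed at the review, on time or late, precedes the switch and has no overlap.

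**2. Is there a route to a form after the switch?** The coordinator's check comes after the site has completed its forms, and phone completion is allowed. A query raised after an on-time review can therefore be answered after hand-over and still fall within 8 weeks. No passage in the article requires first-period forms to be completed before hand-over.

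**3. Illustrative size.** Let q be the share of participants whose first-period form is completed after the switch and reflects only the prosthesis then in use. Assume no carry-over (as the protocol does) and no period effect. For these participants the expected within-person difference is 0, so the mean difference becomes (1 − q) × the true difference.

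The number of participants runs from 30 down to about 20, since 30 × (1 − 0.33) = 20.1 at the anticipated dropout of up to 33%. The count of 4 late forms is an assumption.

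- q = 4/30 = 0.13: difference × 0.87
- q = 4/20 = 0.20: difference × 0.80

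If the definitive trial were sized on the observed difference with the standard deviation held fixed, the required number would be multiplied by 1/(1 − q)². That is 1/0.867² = 1.33 and 1/0.80² = 1.56. Over a wider assumed range:

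- q = 5%: difference × 0.95, number × 1.11
- q = 10%: difference × 0.90, number × 1.23
- q = 20%: difference × 0.80, number × 1.56
- q = 30%: difference × 0.70, number × 2.04

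Under the same 4-form assumption, the first-period completion rate would be overstated by 4/30 to 4/20, or 13 to 20 percentage points. The documents do not allow the size or direction of the effect on the variance to be worked out.

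**The case against.** The strongest defence is that the crossover is tied to an event. The second prosthesis follows the review, so if the review slips to week 6 or 8 the hand-over slips with it. On that reading the 8 weeks are simply a tolerance for a late visit. The participant preference row has the same 4-week ideal and 8-week maximum after the second prosthesis, where no later switch exists, and this fits that reading. Forms are normally completed and checked at visits. One stated purpose of the phone contact is to keep to the time-points, which works against lateness. The schedule figure is not shown, and the full protocol or case report forms may fix the order of steps within a visit.

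Most of this stands. A late review is not a problem, and the ordinary path gives valid scores. What remains is narrower: after an on-time switch, a form retrieved later meets the limit as written, and nothing in the article excludes it. If the limit was meant only for late visits, the correction writes that down.

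A reader might go further and infer that first-period scores will routinely be taken on the wrong prosthesis, or that the feasibility conclusions are at risk. The documents support neither. They give no rate of late completion. The primary outcomes (eligibility, recruitment, conversion and attrition) and the key progression criteria (recruitment and attrition) do not use these questionnaires. The statistical methods plan descriptive analysis without comparisons between groups. Compliance with the trial schedule is itself a secondary feasibility outcome, so lateness is something the study intends to observe.

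**Conclusion.** The point holds in a limited form and is of moderate importance. As written, the Table 1 limit accepts first-period quality-of-life forms for up to 4 weeks after an on-time switch, and the protocol's own reasoning on carry-over implies that such forms do not measure the first prosthesis. The overlap follows directly from the stated times, provided the second prosthesis is delivered at or soon after the 4-week review.

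The size of any effect is unknown. The 13% to 20% dilution rests on an assumed 4 late forms, on each reflecting only the second prosthesis, and on no period effect. Partial recall of the first prosthesis would make the dilution smaller. The multiplier on the definitive sample size applies only if that trial is planned on the observed difference. What is exposed is the set of descriptive estimates, variances and completion rates for the TOMCP-27, SF-12v2 and EQ-5D-5L that feed into that planning.

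**What to change.** In Table 1, split the maximum time for the two prostheses. For the first, allow completion up to 8 weeks after its delivery, provided this is before the second prosthesis is delivered. The 8-week maximum for the second can stay.

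At analysis, compare each form's completion date with the delivery date of the second prosthesis. Leave any first-period form completed after hand-over out of the first-period estimates and variances, and do not count it as completed in the first-period completion rate. The rule needs dates only, so the statistician can stay masked to the treatment groups.

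The article gives 31 January 2023 as the anticipated end of recruitment, so the table change may come too late to alter data collection. The analysis rule can still be applied wherever both dates are held.

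The cost is one line in the table and one date check. The downside is that a few late forms become missing, and the plan does not impute missing data.
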